## Methods

### Recruitment and screening

The trial will be conducted within early help family support and children’s social care services in three local authorities in the North East of England: Newcastle, Durham and North Tyneside. These particular local authorities were selected due to their geographical and service model variability. Participating practitioners within early help family support and children’s social care services will screen all eligible parents on their caseloads for AUDs within routine appointments. To be eligible, parents must be 18 years or over and be able to give informed consent in English. A broad definition of ‘parent’ will be applied wherein any adult who fulfils a parenting role (as identified by the additional early help family support and/or children’s social care assessment) for a child aged 0–17 years will be considered eligible for the study. This includes both mothers and fathers, step parents and other caregivers. Parents who are attending drug and alcohol services; who have severe, chronic or acute mental health problems or are severely distressed; or whose child is placed on an emergency protection order will be ineligible to participate in the study. Social care practitioners will record demographics of all eligible parents and provide details of the reason for social care involvement. The social care practitioner will administer the Alcohol Use Disorder Identification Test – Consumption (AUDIT-C) screening tool, which measures alcohol consumption [55]. The AUDIT-C is a three-item tool that has been found to have comparable sensitivity to the 10-item AUDIT in detecting heavy drinking; it performs better than the 10-item AUDIT in detecting alcohol dependence in women and has greater efficiency in screening hazardous alcohol use in men [56]. The tool was considered to be preferable to the 10-item version for use in early help family support and children’s social care setting. Parents within this setting are likely to be concerned that their parenting capacity will be negatively judged and may therefore be reluctant to provide an accurate response to the dependence and control items of the 10-item AUDIT. Moreover, the use of the AUDIT-C is in-line with usual practice in social care. It has been validated using a cut-off score of ≥ 5 in European general populations [57], men and middle-aged women [58]. Those parents screening positive for AUD on the AUDIT-C (an AUDIT score of ≥ 5) [59] will be invited to participate in the trial by the social care practitioner. The social care practitioner will provide a participant information leaflet to the parent, explain the trial and seek informed written consent for participation. In families where multiple caregivers screen positive and agree to participate, the parents will be recruited as individual cases.

### Randomisation and blinding

The study will employ a cluster randomisation design, with the practitioners being the unit of randomisation. As a single practitioner works with all family members, this will prevent within-family contamination (i.e. if multiple members of one family are recruited to the trial, all family members will receive the same intervention), as well as reducing contamination caused at a practitioner level. The intervention delivered by the early help family support and social care practitioners is provided to the participant immediately following recruited and within the same contact. As such, randomisation will not be compromised by a change in the participant’s allocated practitioner. The practitioners will be randomised to one of the three trial arms in a 1:1 ratio using block randomisation. The study statistician will allocate practitioners to trial arms using a randomised sequence created in Stata 14 [60]. The randomisation will be stratified by a local authority area and practitioner role (early help practitioner, family support worker, social worker within the assisted and support year in employment and progressed social worker), with equal probabilities for each of the three arms and randomly generated varying block size. Service level (early help family support or statutory children’s social care) should be balanced across the strata by the randomisation. Blinding of group allocation will not be possible for the participants or the researcher completing follow-up questionnaires. The study statistician and health economist will be blind to group allocation throughout analysis; participants and practitioners will only be identified by study numbers. Within a definitive trial, researchers, statisticians and health economists will be blinded.

### Sample size

As this is a pilot feasibility trial and not an outcome evaluation, no formal power calculation is required [61]. Rather, the function of a pilot feasibility trial is to provide data that can inform a power calculation for a future definitive trial. For the pilot trial, a minimum of 35 respondents in each trial arm at the 12-month follow-up is required to estimate the critical parameters to the necessary degree of precision for a continuous primary outcome (number of occasions drinking 5+ standard drink units in a single occasion as derived from the TLFB/30) [62]. Attrition of 33% at the 12-month follow-up is generally assumed within feasibility trials [63]. However, due to a paucity of trial-based research conducted with parents involved in early help family support and children’s social care, a cautious 42% loss to follow-up has been applied. Consequently, the sample size to be recruited will be inflated to 60 parents in each of the three arms (Please see Fig. 1).

**Fig. 1 Fig1:**
[figure not shown]
Recruitment flowchart

To achieve this sample, we estimate that social care practitioners within three local authorities will need to approach 921 parents. We expect 84% of parents will meet the inclusion criteria for the trial, similar to rates of eligibility within primary care populations [51]. Based upon Manning et al. [1], we estimate that 30% of parents will score 5 or more on the AUDIT-C and, similar to a brief alcohol intervention trial with pregnant women [49], 78% will provide informed consent to participate in the trial. We estimate that we will need to recruit 45 social care practitioners across the three local authority areas (15 practitioner per local authority, with five practitioners per local authority randomised per trial arm), each approaching 21 parents and recruiting four parents to the trial.

### Consent

Social care practitioners will provide all parents on their caseloads with an information leaflet about the study a minimum of 24 h in advance of conducting alcohol screening. After administering the AUDIT-C, social care practitioners will explain the study to eligible parents who screen positive for an AUD and answer any questions they may have. If the parent decides to participate, they will be asked to provide written consent, which will be recorded on a consent form (please see consent form in the Additional file 1: Appendix). Additional consent will also be sought for qualitative interviews which will be conducted within the process evaluation, and audio-recording of intervention sessions (to enable fidelity assessments). The consent form will include a unique identifier which enables the consent to be linked to the anonymised personal data gathered within the baseline questionnaire.

### Baseline and follow-up procedure

After informed consent has been obtained, but before intervention delivery, the social care practitioner will collect baseline information from the parent. All participants who completed baseline questionnaires will be contacted by telephone, letter or email by a member of the research team, at 6 and 12 months post recruitment, and invited to complete a follow-up questionnaire. A response window of 8 weeks will be in place to maximise follow-up. Participants who do not complete the 6-month follow-up will still be invited to complete the 12-month follow-up. The questionnaire will be administered in person or over the phone by the researcher or self-completed via post, email or the web (depending upon participant preference). If after a minimum of three repeated attempts the researcher is not able to contact the participant by their preferred method, alternative methods will be attempted (telephone, postal or email contact). Where all attempts to contact the participant fail, effort will be made to make contact with the participant via the recruiting social care practitioner.

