**Methods:**

The cluster randomised controlled trial will be conducted within early help family support and children’s social care services in three local authorities in the North East of England: Newcastle, Durham and North Tyneside. All eligible parents the caseloads of participating practitioners will be screened for an AUD using the Alcohol Use Disorder Identification Test – Consumption (AUDIT-C) screening tool by the social care practitioners within routine appointments. All parents who score 5 or more on the AUDIT-C will be invited to participate in the trial. Consenting participants will complete a baseline questionnaire before receiving one of three randomised interventions: (i) healthy lifestyle leaflet (control intervention); (ii) a brief alcohol advice intervention delivered by the social care practitioner plus healthy lifestyle leaflet; (iii) a brief alcohol advice intervention delivered by the social care practitioner, healthy lifestyle leaflet plus a 40-min behaviour change intervention with an optional review session delivered by the local alcohol service. Follow-up data will be collected 6 and 12 months post recruitment. A linked qualitative study will explore participating parent and practitioner views on the acceptability of trial processes and interventions.

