A clear success criteria (‘go’) would be meeting of all of the targets of recruitment of three local authorities as research sites from within the North East region of England; ≥ 60% of eligible participants consenting to pilot feasibility trial; ≥ 60% of consenting participants accepting/attending intervention sessions; retention of ≥ 60% of consented participants for provision of key outcome data at 12 months. These are common parameters considered when decided upon progression to definitive trial [50]. Whilst within randomised controlled trials of brief alcohol interventions in primary care settings often report a consent rate of 80% and aim to retain 70% of participants at the 12-month follow-up [51], parents involved in early help family support and children’s social care are a vulnerable population and external factors within their daily living may reduce the likelihood of providing consent to participate in the trial and of being retained at follow-up. As such, more cautious success criteria have been suggested. Receipt of interventions delivered opportunistically is typically high in trials of brief interventions (99%); however, attendance at scheduled brief interventions wherein a participant is required to return at a later date for an appointment is much lower (around 50–60%) [51–53]. To allow for this variation between interventions, the intervention will be considered to have met the success criteria if ≥ 60% of randomised participants in each arm receive the intervention. Where marginal results are reached (recruitment of two local authorities; 59–40% of eligible participants consenting to pilot feasibility trial; retention of 59–50% of consented participants at 12 months; 59–30% of participants receiving a randomised intervention), a process for decision making after pilot and feasibility trials (ADePT) [54] will be followed, systematically appraising the problems and potential solutions within the linked process evaluation.

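### Follow-up contact is scheduled for baseline completers, but retention is judged on all who consented, so any consenter without a baseline would count as lost without being contacted

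*Protocol article*

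**What the plan says.** Three statements in the protocol article bear on this point.

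- **Order of events.** Under Baseline and follow-up procedure: "After informed consent has been obtained, but before intervention delivery, the social care practitioner will collect baseline information from the parent". Baseline is therefore a separate step after consent.
- **Who is contacted.** For both follow-up points, the same section continues: "All participants who completed baseline questionnaires will be contacted by telephone, letter or email by a member of the research team". It adds that missing the 6-month questionnaire does not stop the 12-month invitation. It has no matching provision for a missed baseline.
- **Who is counted.** The Aim section sets the go criterion as "retention of ≥ 60% of consented participants for provision of key outcome data at 12 months" and the marginal band as "retention of 59–50% of consented participants at 12 months". Both use consented participants as the denominator.

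The Sample size section names a continuous outcome, the number of heavier drinking occasions derived from the timeline follow-back. Under Measures and in Table 1, that instrument is given at 12 months only.

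**The concern.** The contact sentence is limited to people with a completed baseline, while the progression criterion counts everyone who consented. A consenter without a baseline would fall between the two: not scheduled for contact at either time point, but included in the denominator as not retained.

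Estimating retention is an objective of this pilot, and retention is one of the criteria for moving to a definitive trial. The figure should show whether parents in this setting can be followed for 12 months. Losses produced by the contact wording say nothing about that, but they would lower the figure all the same. They would also give up usable data, because a parent with no baseline can still complete the timeline follow-back, and the alcohol problems and service-use questionnaires are likewise given only at follow-up.

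**Working it through.** **The plan's own figures first.**

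- Sample size section: at least 35 respondents per arm at 12 months and 42% loss. 35 / (1 − 0.42) = 60.3, against 60 per arm stated, or 3 × 60 = 180 in all. This reproduces apart from rounding.
- Recruitment estimate in the same section: 921 approached, 84% eligible, 30% screening positive, 78% consenting. 921 × 0.84 × 0.30 × 0.78 = 181.0, against 180. This reproduces. The chain runs from consent straight to the recruited sample, with no step for baseline non-completion.

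The mismatch affects neither figure.

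**Effect on the retention criterion.** Let *b* be the share of consenters who do not complete the baseline, and *r* the 12-month retention among those contacted. If people without a baseline are not contacted and supply no outcome data:

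retention among consented = (1 − *b*) × *r*

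so the *r* needed is 0.60 / (1 − *b*) for the go line and 0.50 / (1 − *b*) for the lower edge of the marginal band. The article gives no value for *b*; every non-zero value below is an assumption.

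| Assumed *b* | Not scheduled for contact, of 180 | *r* needed for 60% of consenters | *r* needed for 50% of consenters |
|---|---|---|---|
| 0% | 0 | 60.0% | 50.0% |
| 5% | 9 | 63.2% | 52.6% |
| 10% | 18 | 66.7% | 55.6% |
| 20% | 36 | 75.0% | 62.5% |

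Check by counts: 60% of 180 is 108 participants, and 108/171 = 63.2%, 108/162 = 66.7%, 108/144 = 75.0%.

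If all consenters are contacted, the wording adds no loss of its own and the requirement stays at 60% for any *b*.

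**The case against.** The strongest reply is that the two groups are meant to be the same people. The abstract says "Consenting participants will complete a baseline questionnaire before receiving one of three randomised interventions". Under Randomisation and blinding, the practitioner's intervention "is provided to the participant immediately following recruited and within the same contact", so consent, baseline and intervention follow one another in a single visit. The recruitment estimate has no baseline-loss step. The contact sentence does not contain the word only, and a questionnaire with a few blank items may well count as completed. Handling of a missing baseline could also be covered in the full protocol, which is not shown.

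Much of this stands. It makes the effect conditional, and at *b* = 0 there is none. It does not remove the point. The Aim section lists response to the baseline questionnaire among the rates to be estimated, so complete baseline data is not taken for granted. The contact sentence is restrictive as worded, and the one exception in that section is for a missed 6-month follow-up.

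A second reply is that local authority records are collected at 6 and 12 months without contacting the parent, so a consenter without a baseline might still supply data. The Aim section does not say whether those records count as key outcome data, so this remains open.

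A third is that consented participants are the right, conservative denominator. That is correct. The weakness lies in the contact wording, not in the criterion.

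**Conclusion.** The point holds in a limited form. The article names one group for follow-up contact and a wider one for judging retention. If any consenter lacks a completed baseline, that person counts as lost without being scheduled for contact. The size depends entirely on a rate the article does not give: the retention needed among those contacted rises from 60% to 63.2%, 66.7% or 75.0% at assumed non-completion of 5%, 10% or 20%. This also assumes that the sentence is applied literally and that record data do not count towards retention.

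A reader might infer more than the article supports:

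- **That some consenters can never be retained.** This presumes both a strict exclusion and actual baseline non-completers; the article states neither.
- **That each arm will fall below 35 respondents.** Applying the planned 58% to a number already reduced for missing baselines may count loss twice, because the 42% is applied to everyone recruited.
- **That loss will differ by arm.** Practitioners know their arm, but nothing in the article shows that baseline completion would vary with it.
- **That intention-to-treat is breached.** This carries little weight in a pilot that tests no hypothesis and whose planned analysis is descriptive.

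It remains worth changing, because the correction is nearly free and protects a figure that feeds the progression decision.

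**What to change.** In Baseline and follow-up procedure, replace the sentence on who is contacted with: *All consented participants who have not withdrawn will be contacted by the research team at 6 and 12 months, whether or not the baseline questionnaire was completed.* The listed contact methods can stay as they are.

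Leave the denominator in the Aim section unchanged, as consented participants, for both the go criterion and the marginal band.

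The cost is one sentence, a few extra follow-up contacts, and some participants with 12-month data but no baseline values. Those participants can enter the retention figure and the 12-month timeline follow-back summary, but not summaries of change from baseline.

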### Measures

The following measures will be administered at baseline and at both follow-ups:Remaining 7 questions of the *AUDIT*, 10-item tool, will be used to measure alcohol problems. The AUDIT is the *gold standard* alcohol screening tool [64]. In addition, participants will be asked to state their average weekly spend on alcohol.Family functioning will be assessed with the *family perceptions scale* (FPS). The FPS is a 29-item tool across five domains (nurture, problem solving, expressed emotion, behavioural boundaries and responsibility) [65]Mental health and well-being will be assessed using the *Warwick Edinburgh Mental Well-Being Scale* (WEMWBS). The WEMWBS is a 14-item scale of mental well-being covering subjective well-being and psychological functioning, in which all items are worded positively and address aspects of positive mental health. The tool has been used extensively with adults [66]Health-related quality of life (HRQoL) will be assessed using the *European Quality of Life—5 Dimensions—5 Levels* (EQ-5D-5L) instrument. EQ-5D has been developed by the EuroQol Group to provide a simple, generic measure of health for clinical and economic appraisal, where health is characterised on five dimensions (mobility, self-care, ability to undertake usual activities, pain, anxiety/depression) [67].

The following measures will be administered at the 6- and 12-month follow-up:*Alcohol problems questionnaire*—this is a clinical instrument for measuring alcohol-related problems. It has been used to study the relationship between alcohol-related problems and dependence within the bi-axial model [68]A modified *Client Service Receipt Inventory—*this is a tool used to comprehensive assess service usage to enable economic analysis [69]Local authority system-held information relating to case allocation, legal and care status of the child will be collected from children’s social care at the 6- and 12-month follow-up.

The following measure will be administered at the 12-month follow-up only:*30-day timeline follow back* (TLFB30). The TLFB30 is an established valid and reliable method of ascertaining alcohol consumption in adult populations over a reference period ranging from 7 to 365 days [70].

Please see Table 1 for further details.

**Table 1 Tab1:** Schedule of events

Study period						
Research phase	Recruitment	Baseline	Session 1	Session 2	6-month follow-up	12-month follow-up
Informed consent	X					
Demographics		X				
Eligibility assessment	X	X				
AUDIT (AUDIT-C as screening tool; remaining questions of 10-item tool administered at baseline)	X					
Control group Healthy lifestyle leaflet	X					
Intervention 1 Brief alcohol advice plus healthy lifestyle leaflet	X		X			
Intervention 2 Extended alcohol intervention plus brief alcohol advice plus healthy lifestyle leaflet	X		X	X		
AUDIT (10-item)		X			X	X
Estimated spend per week on alcohol		X			X	X
WEMWBS		X			X	X
EQ-5D-5L		X			X	X
FAD		X			X	X
TLFB-30						X
APQ					X	X
Use of health and social services					X	X
Case allocation, legal and care status					X	X
Qualitative interviews with participating practitioners					X	X^a^
Qualitative						

^a^Qualitative interview participants will be interviewed on one occasion only at varying stages of the follow-up

All identifiable data collected will be separated from personal data to maintain confidentiality and a unique reference number allocated to enable data linkage across sources and time periods. All data will be stored on a secure server, with identifiable data being password protected and stored.

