### Economic evaluation

The purpose of a definitive economic evaluation is to assess benefits as well as costs to patients and their families/carers, the NHS and personal social services (societal perspective). Health economic assessment will consider real costs (training of practitioners, screening of parents, intervention delivery) and outcomes (reduced alcohol consumption, reduced problems, service usage). Data on health consequences will be collected by means of participant completed questionnaires collected at baseline and the 12-month follow-up to capture changes in health-related quality of life outcomes (measured by EQ-5D-5L). Responses to the EQ-5D-5L will be used to calculate quality adjusted life years (QALYs). The CSRI will be modified for the definitive trial in response to data collected within the current study, to make it relevant to the study population. The associated costs will relate to resources required to provide the intervention and usage of NHS, public and personal social services and patient cost during the follow-up period. We will ascertain data completeness of the instruments and any potential bias in the completion of follow-up data to inform the choice of instruments in a future trial. The majority of the outcome data will be presented in simple descriptive tables presenting percentages, means and standard deviations or five-number summary (as appropriate), for each arm of the study. The findings from the pilot feasibility trial will then be incorporated into a probabilistic mathematical decision analytic model to provide preliminary estimates of cost, effectiveness and relative cost-effectiveness and assess the value of information (VoI) for a definitive study. The VOI will be used to inform the design, choice of primary outcome, necessary sample size and approach to the analysis, of the future definitive trial. The VOI will also be used to estimate the expected value of sampling information (EVSI). The EVSI will quantify the value of reducing uncertainty via collection of additional data in a definitive trial.

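### The article contradicts itself on follow-up data: which AUDIT items are asked, which EQ-5D-5L time points feed the QALYs, and which family instrument is used

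*Protocol article*

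**What the plan says.** **AUDIT.** The Measures section introduces its first list with "The following measures will be administered at baseline and at both follow-ups:Remaining 7 questions of the" AUDIT. Table 1 has two AUDIT rows. One, marked only under Recruitment, reads "AUDIT (AUDIT-C as screening tool; remaining questions of 10-item tool administered at baseline". The other is the 10-item AUDIT, marked at baseline, 6 months and 12 months. Under Recruitment and screening, "The AUDIT-C is a three-item tool" that measures consumption. Under Consent it comes before recruitment: "After administering the AUDIT-C, social care practitioners will explain the study to eligible parents who screen positive for an AUD". The timeline follow-back (TLFB30) is introduced by "The following measure will be administered at the 12-month follow-up only".

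**EQ-5D-5L.** Measures puts it in the list for baseline and both follow-ups ("Health-related quality of life (HRQoL) will be assessed using the" EQ-5D-5L), and Table 1 marks the same three time points. The Economic evaluation section says that data on health consequences are "collected by means of participant completed questionnaires collected at baseline and the 12-month follow-up to capture changes in health-related quality of life outcomes". The instrument for this is the EQ-5D-5L, and the next sentence of that section derives QALYs from its responses.

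**Family functioning.** Measures says "Family functioning will be assessed with the" family perceptions scale (FPS), and the abbreviations list includes FPS. Table 1 has no FPS row. It has a row labelled FAD, which the article does not define.

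**The concern.** The text and Table 1 cannot both be followed for the AUDIT. The seven items are the remaining ones only at baseline, when the three AUDIT-C items have just been asked at screening. At 6 and 12 months there is no fresh AUDIT-C for them to complete.

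The pilot has to estimate response to the outcome measures (Aim) and describe their variability (Statistical analyses), and the definitive trial's primary outcome is still to be chosen. The Economic evaluation section counts reduced alcohol consumption among its outcomes, and showing a reduction needs the same instrument before and after. TLFB30 has no baseline, so the AUDIT consumption items are the only direct drinking measure that could supply both values.

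The QALYs matter because the pilot's findings go into the decision model and the value-of-information analysis, which is meant to inform the choice of primary outcome and the sample size of the definitive trial. If month 6 is left out, collected data go unused and any change that comes and goes within the year is not seen.

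**Working it through.** No stated figure in the plan is at issue, so there is none to reproduce. The check compares the sections and then adds a short calculation for the QALYs.

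**1. Schedule by source**

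| Item | Measures text | Table 1 | Economic evaluation |
|---|---|---|---|
| AUDIT at baseline | 7 items, after AUDIT-C at screening | 10-item | not stated |
| AUDIT at 6 and 12 months | 7 items | 10-item | not stated |
| EQ-5D-5L | 0, 6, 12 months | 0, 6, 12 months | 0, 12 months |
| Family instrument | FPS | FAD | not stated |

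On the AUDIT, the text conflicts with Table 1. On EQ-5D-5L, those two agree and the economic section differs from both.

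**2. What remains if the text is followed for the AUDIT**

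- Items not repeated at follow-up: 10 − 7 = 3, all of them the consumption items.
- Baseline: AUDIT-C (from screening), AUDIT total, weekly spend on alcohol.
- 6 months: seven AUDIT items, weekly spend, alcohol problems questionnaire. No direct measure of quantity or frequency.
- 12 months: the same, plus TLFB30, which has no baseline counterpart.

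So no direct drinking measure is paired over time. Weekly spend is paired, but it is a proxy. Under Table 1 the three items return at both follow-ups, and the AUDIT total and AUDIT-C are paired.

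**3. Number affected.** Planned recruitment is 3 × 60 = 180. The plan needs 35 respondents per arm at 12 months, so 3 × 35 = 105. As a check, 180 × (1 − 0.42) = 104.4. The relevant number at 12 months is about 105.

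**4. QALYs with and without month 6.** Let u0, u6 and u12 be the utilities at 0, 6 and 12 months, with area under the curve by trapezoids over one year.

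- Three points: 0.25·u0 + 0.50·u6 + 0.25·u12
- Two points: 0.50·u0 + 0.50·u12
- Difference: 0.5 × [u6 − (u0 + u12)/2]

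The article gives no utilities, so those below are assumptions.

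| u0, u6, u12 | Two-point | Three-point | Difference |
|---|---|---|---|
| 0.70, 0.75, 0.80 (linear) | 0.750 | 0.750 | 0 |
| 0.70, 0.75, 0.70 | 0.700 | 0.725 | +0.025 |
| 0.70, 0.80, 0.70 | 0.700 | 0.750 | +0.050 |
| 0.70, 0.65, 0.70 | 0.700 | 0.675 | −0.025 |
| 0.70, 0.60, 0.70 | 0.700 | 0.650 | −0.050 |

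These are shifts for one participant. A comparison between arms moves only by the difference in mean shift, so a departure common to both arms cancels.

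**The case against.** The case for treating this as a drafting slip is good. Measures ends by sending the reader to Table 1, which marks the 10-item AUDIT at both follow-ups. Its screening row also explains where the seven-item split comes from. The natural reading is that baseline wording was placed under a heading that also covers follow-up. The continuous outcome used for sizing comes from TLFB30, which the AUDIT wording does not touch, and the pilot tests no hypothesis.

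On QALYs, the economic section names two time points but does not exclude the third, and the sentence on QALYs sets no time limit. The detailed calculation may sit in a document that is not shown.

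Most of this stands, and it limits the point. A reader might infer that the trial will lose consumption data for all 180 participants, that nothing bearing on drinking is collected at 6 months, or that QALYs are fixed as two-point with a loss of 0.05. The article does not support these inferences. Table 1 points to the full AUDIT, weekly spend is collected at 6 months, about 105 participants are expected at 12 months, the two-point QALY is only inferred, and 0.05 belongs to one assumed trajectory.

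The contradictions themselves remain. Detail left to another document would be no finding, but here the article states instruments and times and states them differently in different places. The FAD label is minor. APQ is also missing from the abbreviations list, but the text names that instrument in full, whereas nothing in the article explains FAD.

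**Conclusion.** The point holds as an internal contradiction that should be corrected. It does not show that data will be lost.

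- **AUDIT:** the consequence is conditional. Only if the questionnaire follows the Measures text are there no AUDIT total and no AUDIT-C at 6 and 12 months, and no direct drinking measure with a baseline and a follow-up value. Table 1 makes that the less likely reading, but the article alone cannot settle which form is in use.
- **QALYs:** two of the three collected time points are named. The effect of omitting month 6 is zero under linear change and 0.025 to 0.05 per participant, in either direction, for an assumed departure of 0.05 to 0.10.
- **Family instrument:** a labelling mismatch with no demonstrated effect on analysis, though a reader cannot tell from Table 1 which scale is given.

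**What to change.** 1. In Measures, state that the seven remaining items complete the screening AUDIT-C at baseline and that the full 10-item AUDIT is given at 6 and 12 months. Check the questionnaire in use against this. The cost is a wording change and at most three extra items per follow-up. The check is time-critical: recruitment began in October 2017, so the first 6-month follow-ups could have fallen around April 2018, before publication in June 2018. Items already missed at a 6-month follow-up cannot be recovered.
2. In Economic evaluation, state that QALYs use the area under the curve over baseline, 6 and 12 months. The 6-month EQ-5D-5L is already scheduled, so this needs no extra data collection.
3. Name one family instrument throughout, by correcting either the FAD row in Table 1 or the FPS text. This is a wording change once the form in use has been confirmed.
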